## Abstract

**Background:**

Cladribine tablets (marketed as Mavenclad) are a new oral therapy, which has recently been listed on the pharmaceutical benefits scheme in Australia for the treatment of relapsing multiple sclerosis (MS). The current dosing schedule is for 2 courses given a year apart, which has been shown to be effective for treatment of MS for up to 4 years in 75% of patients (based on annualized relapse rate). However, the reinitiation of therapy after year 4 has not been studied.

**Objective:**

This study aims to evaluate the safety and efficacy of cladribine tablets over a 6-year period, according to no evidence of disease activity 3.

**Methods:**

This will be a multicenter, 6-year, phase IV, low interventional, observational study that incorporates clinical, hematological, biochemical, epigenetic, radiological and cognitive biomarkers of disease. Participants considered for treatment with cladribine as part of their routine clinical care will be consented to take part in the study. They will be monitored at regular intervals during the initial course of medication administration in years 1 and 2. After year 3, patients will have the option of redosing, if clinically indicated, or to switch to another disease-modifying therapy. Throughout the duration of the study, we will assess blood-based biomarkers including lymphocyte subsets, serum neurofilament light chain, DNA methylation, and RNA analysis as well as magnetic resonance imaging findings (brain volume and/or lesion load) and cognitive performance.

**Results:**

This study has been approved by the Hunter New England Local Health District Human Research Ethics Committee. Recruitment began in March of 2019 and was completed by June 2021.

**Conclusions:**

This will be the first long-term efficacy trial of cladribine, which offers reinitiation of therapy in the 3rd year, based on disease activity, after the initial 2 courses. We expect that this study will indicate whether any of the assessed biomarkers can be used to predict treatment efficacy or the need for future reinitiation of cladribine in people with MS.

**Trial Registration:**

This study is registered with the Australian and New Zealand Clinical Trials Registry (ACTRN12619000257167) with Universal Trial Number (U1111-1228-2165).

**International Registered Report Identifier (IRRID):**

DERR1-10.2196/24969

## Introduction

### Overview

Multiple sclerosis (MS) is a common, immune-mediated, demyelinating disease that affects the central nervous system. MS has a highly variable course; therefore, patient-specific treatment decisions are becoming increasingly important. Currently, we have no way to differentiate between the patients who will acquire rapid disability progression and the ones who will remain stable over several years. Most studies point toward early intervention giving a better long-term outcome; however, long-term immunosuppression is associated with increased adverse risk [1,2]. Generally, MS therapies are long-term and some have a demonstrated rebound phenomenon precluding them from being stopped for long periods of time, such as fingolimod [3] and natalizumab [4]. However, there are currently 2 drugs that can potentially be used for immune reconstitution treatment: alemtuzumab and cladribine.

Alemtuzumab is administered in 2 courses, via infusion, 1 year apart. In the Comparison of Alemtuzumab and Rebif Efficacy in Multiple Sclerosis Study (CARE-MS) extension trial, a redosing scheme was introduced, with up to 4 additional doses being offered in the event of recurring clinical activity [5]. Cladribine is a synthetic purine analog, and its mechanism of action is thought to be primarily via induction of apoptosis in lymphocytes [6]. It was shown in a phase III trial (A Safety and Efficacy Study of Oral Cladribine in Subjects with Relapsing-Remitting Multiple Sclerosis; CLARITY) to be highly effective in controlling disease activity [7-10]. With a no evidence of disease activity 3 (NEDA 3) rate of 44% over 2 years [7], it is placed in the range of the most efficacious disease-modifying therapies (DMTs) along with alemtuzumab (39%) [11,12] and ocrelizumab (47%) [13]. Furthermore, after 2 years of treatment and 2 years of follow-up (treatment free), 75% of patients with MS remained relapse free [8,14]. However, clinical stability beyond year 4, and additional doses of cladribine tablets based on clinical activity, has not yet been studied.

In the study discussed below*,* we will offer additional doses of cladribine tablets after 3 years. We aim to compare the clinical outcomes of patients with MS who received additional doses of cladribine with those who changed DMT. We also aim to identify biomarkers for disease control that can be used for treatment decisions, such as redosing with cladribine tablets versus change of DMT.

### Justification of Outcome Measures: NEDA

With the introduction of an ever-increasing number of DMTs, our treatment goals have shifted from simply reducing relapses to achieving *NEDA*.

In MS, NEDA 3 is defined as no clinically confirmed progression, no relapse, and no new or enlarging or gadolinium (Gd)-enhancing lesions [15]. This has since been expanded to NEDA 4, which includes brain atrophy [16]. Although our current treatments are increasingly effective, only 30% of patients with MS reach NEDA 4 after 2 years [17]. The rate of NEDA 4 in patients with MS treated with cladribine has not yet been established.

### Magnetic Resonance Imaging for Assessing Progression of MS

Magnetic resonance imaging (MRI) has been established as the most reliable indicator of long-term outcomes. Sormani et al [18] analyzed data from 13 large clinical trials, including 13,500 patients with MS, to show that new T2 lesions can predict disability progression. This prediction was significantly improved when combined with brain atrophy [18]. Some of the high efficacy treatments can change the rate of brain volume loss to that seen in the normal aging population [19]. As MRI technology advances, it has become clear that some substructures such as thalamic volume, lateral ventricle, and gray or white matter volume might be even more sensitive and correlate better with clinical outcomes [20].

### Lymphocytes as Biomarkers

Blood-based biomarkers are attractive because of their ease of collection and cost-effectiveness. In addition, they may better reflect or even predict disease activity. Lymphocyte subsets may be good markers of disease stability, as many currently used therapies act by restoring the balance of immune cells in the periphery to a *healthy* state. Therapies affecting the B-cell population have been described as effective treatments for MS [21]. This may be related to the suppression of memory B cells. This theory is supported by the failure of Atacicept and tumor necrosis factor α inhibitors in treating MS, both of which result in disease activation [21]. In both ORACLE-MS and CLARITY, cladribine has been shown to markedly reduce B cells, while having a more modest reduction in T cells and natural killer cells [22,23]. A more recent study of the CLARITY cohort further characterized this reduction and demonstrated that memory B cells were the predominantly affected subtype [24].

These studies investigated lymphocyte subsets over the course of 1-2 years. Therefore, a long-term investigation of lymphocyte subsets in response to cladribine treatment is warranted.

### Cognitive Dysfunction in MS

Cognitive impairment is a prevalent symptom in MS, with rates of approximately 40%-70% [25]. The severity of cognitive deficits varies, but unlike the physical symptoms associated with MS, cognitive deficits are unlikely to remit and are associated with a higher risk of progression [26-28]. A recent systematic review evaluated the literature on cognitive impairment and employment status and found a consensus that patients with MS who are unemployed or have reduced work hours record weaker cognitive scores [29]. Loss of employment is a major concern for patients with MS, particularly as the disease is often diagnosed in people of working age, who are just establishing careers and families. Despite this, cognitive testing is often disregarded in terms of clinical trial outcomes. Several tools have been developed to evaluate cognitive function, including the Brief Cognitive Assessment for Multiple Sclerosis (BICAMS) [30]. The BICAMS is quick and easy to administer and has recently been validated in the Australian population [31].

### Global Epigenetic Profiles in MS

Epigenetics is a rapidly developing area of medical research and refers to the potentially reversible regulation of genomic functions, particularly gene expression. This provides a mechanism whereby an organism can dynamically respond to a change in its environment (eg, DMTs) and alter its gene expression accordingly. DNA methylation is a well-characterized, relatively easy to study epigenetic modification and generally refers to the addition of a methyl group to a cytosine base, followed by a guanidine (referred to as a CpG dinucleotide).

We, and others, have described differential DNA methylation profiles between healthy controls and patients with MS, as well as between relapsing remitting MS and secondary progressive MS [32-38]. In addition, we and others have performed longitudinal studies that found epigenetic profiles are altered after dimethyl fumarate treatment [39-41], making it a potentially specific biomarker for treatment response.

### Neurofilaments are a Promising Biomarker

Neurofilament (NfL) light chains are found in neuronal cells but are shed into the cerebrospinal fluid upon neuronal damage and are detectable in the peripheral blood. Increased serum NfL levels have been identified in patients with MS compared with that in healthy controls [42]. These levels show a strong correlation not only with cerebrospinal fluid NfL levels but also with the presence and activity of focal lesions and clinical outcomes [42]. This makes them a promising biomarker not only of disease activity but also disease progression. These may be useful indicators of the need for additional courses of treatment.

### Objective

The primary objective of the study is to evaluate the safety and efficacy of cladribine tablets over a 6-year period according to NEDA 3. We will also evaluate clinical outcomes and cognition over a 6-year period, blood-based and MRI-based biomarkers for their ability to predict treatment response, disease activity, and the need to redose cladribine subsequent to the 2-year, 2 initial courses.

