## Methods

### Study Design

This study is a multicenter, 6-year, phase IV, low interventional trial. Enrollment of 150 patients with MS was planned across 9 specialist MS clinics in Australia. The Therapeutic Goods Australia approved a cumulative dose of cladribine (10 mg) tablets as 3.5 mg/kg body weight over 2 years administered as 1 treatment course of 1.75 mg/kg per year. After 3 years, patients with MS in consultation with their health care provider will discuss the option of redosing with cladribine tablets, if clinically indicated (by relapse or new MRI activity), switch to another DMT, or continue without change (without commencement of any DMT). For those who will be continued on cladribine, additional courses will be administered as per the previous dosing of 1.75 mg/kg per year.

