### End Points

The primary end point for all outcome measures is the proportion of patients with MS achieving NEDA status (responders) at 6-years relative to screening. However, preliminary end points will also be considered at each of the major biomarker collection points (months 7, 24, 48, and Tv).

The key outcome measures will be NEDA 3 or 4 responders after 6-years. Additional outcome measures will change over time from baseline in MRI parameters (brain volume loss, lesion load, and lesion volume), cognition, lymphocyte subsets, sNfL, and global DNA methylation profiles. In addition, the Tv time point will be used to determine if there are any changes in biomarker status that may predict disease activity. This will be compared with the time point at which the patient is deemed to have stable disease.

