#### Association Modeling

Our primary outcome is treatment response status according to NEDA 3. We will perform parametric statistical analysis to determine whether any clinical parameters are associated with outcome—the dependent variable. Multiple repeated measurements of the same individual will be obtained. Therefore, we will apply generalized linear mixed models for binary outcomes, with random effects for time points to account for within-subject correlations and clustering. Clinical factors included in the primary analysis will be EDSS, MRI, and relapse rate measures regressed at baseline. Confounding factors (age, sex, disease duration, etc) will be included as required. By carefully defining covariate values in terms of lagged or leading indicators of study factors, longitudinal data will help us to establish the direction of causation and any lags involved. We will also use Mendelian randomization techniques to help dissect causation from the correlation of evidence for causality. In this analysis, all predictor biomarker variables will be modeled individually and yield a test-specific (unadjusted) *P* value. However, we will apply a Benjamini-Hochberg false discovery rate to adjust the raw *P* value for multiple testing while maintaining power. The secondary outcome variables will be modeled similarly using mixed models with specific parameters dependent on the type of data.

To identify multi-biomarker signatures that predict response in this patient cohort, we will also use machine learning algorithms on the patient cohort data set. Specifically, elastic-net regularized generalized linear model analyses using logistic, linear, or multinomial or Poisson models (depending on the outcome variable) will be conducted within a cross-validation routine to avoid overfitting. This will be performed on the entire factor set using the GLMNet package in the R program [46]. Briefly, GLMNet fits a generalized linear model via penalized maximum likelihood and is akin to a stepwise forward regression with the added feature of being able to perform internal cross-validation. GLMNet allows for both binary and multinomial outcomes. GLMNet allows for the rapid discovery of reduced factor panels that are likely to be associated with outcomes. This complementary approach is not susceptible to multiple testing burdens and will facilitate the identification of the best fitting multifactor signature that is predictive of treatment response [46].

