In the CLARITY study, 75% of the participants were treatment-naïve before entering [7]. As with all pharmaceutical trials, there were restrictions on prior DMT use (no more than two failed DMTs were allowed before study entry, and anyone who had used prior immunosuppression was excluded) [7]. This leaves a scarcity of data relating to how patients with MS who have been on prior DMTs, particularly immune suppressants with long-term effects such as alemtuzumab or even dimethyl fumarate, will respond to cladribine tablets. In addition, this does not reflect clinical reality, where many patients with MS have trialled several treatments and often failed several other DMTs before starting cladribine tablets. Data on the safety and effectiveness of cladribine after other DMTs are needed for clinicians and patients with MS to be able to make appropriate decisions about therapy, particularly if they are switching from a prior immunosuppressant. Our study is well-positioned to provide such data.

This trial will also investigate the effectiveness of additional courses of cladribine tablets based on disease activity. Alemtuzumab, another immunomodulatory therapy, is administered in a similar dosing scheme to cladribine tablets [12]. In the CARE-MS II trial, up to four additional courses of alemtuzumab were given to patients with MS as required, with success [5]. Starting in year 3, if patients with MS in this trial have a clinical or radiological relapse, they will be offered an additional course of cladribine. Although the CLARITY extension trial found that additional courses provided no additional benefit, these courses were not offered based on disease activity [9]. This will be the first investigation into an additional cladribine dose based on disease activity.

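### The need to redose is a stated prediction target but has no outcome of its own: the fixed end point is NEDA counted from screening, much of it settled before redosing can open, and the Tv comparison fills the gap only partly

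*Protocol article*

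**What the plan says.** The Objective section names three targets for the blood and MRI biomarkers: treatment response, disease activity, and "the need to redose cladribine subsequent to the 2-year, 2 initial courses". The Abstract's Conclusions repeat the last one, expecting to learn whether any biomarker "can be used to predict treatment efficacy or the need for future reinitiation of cladribine", and so does the close of Principal Findings in the Discussion.

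The outcome is fixed elsewhere. End Points states: "The primary end point for all outcome measures is the proportion of patients with MS achieving NEDA status (responders) at 6-years relative to screening". Association Modeling adds: "Our primary outcome is treatment response status according to NEDA 3".

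Study Design describes what happens after the initial courses: a consultation on "redosing with cladribine tablets, if clinically indicated (by relapse or new MRI activity), switch to another DMT, or continue without change". The opening date is given in two ways. Study Design has "After 3 years, patients with MS in consultation with their health care provider will discuss the option of redosing with cladribine tablets"; Principal Findings has "Starting in year 3, if patients with MS in this trial have a clinical or radiological relapse".

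There is also a variable time point, Tv. Under End Points and Outcomes it is sampled at an exacerbation and/or before a treatment change or redosing. Under End Points, biomarkers at Tv are compared with those at a time of stable disease, to look for changes that may predict disease activity. Months 7, 24, 48 and Tv are listed as preliminary end points.

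**The concern.** NEDA status counted from screening and the need for a further course are different quantities. A patient with one relapse at month 5 and nothing later is a nonresponder for the whole study, yet never meets the stated indication once redosing is open. NEDA 3 as set out under NEDA Status also includes confirmed disability worsening, which is not part of the indication in Study Design.

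On the reading that status counted from screening cannot be regained, every failure during the two planned courses stays in the 6-year label. A marker associated with that label may reflect early failure, in the window that the initial courses are meant to treat, and not activity arising after them. At stake is the claim that the study can guide decisions on redosing, which is one of its stated reasons for collecting the biomarkers.

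**Working it through.** **Inputs**
- 150 enrolled, at most 20% dropout, about 50% nonresponders (Sample Size Calculation).
- 2-year NEDA 3 rate on cladribine: 44% (Introduction, Overview) and 47% (Discussion, Principal Findings). Both are given for the same trial and they conflict; either serves here.
- Redosing opens after 3 years (Study Design) or from year 3 (Principal Findings). The earliest possible reading is month 24.
- The article gives no 6-year NEDA rate for cladribine, so this is varied.

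**1. The plan's own figures.** 150 × (1 − 0.20) = 120 evaluable; 120 × 0.50 = 60 nonresponders. Both reproduce. The 80% power came from a simulation whose standard deviation and number of tests are not given; nothing here depends on it.

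**2. Status lost by month 24.** 1 − 0.44 = 0.56 and 0.56 × 120 = 67.2; 1 − 0.47 = 0.53 and 0.53 × 120 = 63.6. So about 64-67 of 120 patients have failed by then, already more than the 60 expected in total.

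**3. Share of all 72-month failures that this represents.** Share by month t = (1 − S(t)) / (1 − S(72)), where S is the proportion still NEDA-free. With a constant hazard, S(t) = S(24)^(t/24):
- From 44%: S(36) = 0.44^1.5 = 0.292 and S(72) = 0.44^3 = 0.085. Shares: 0.560/0.915 = 61% by month 24, 0.708/0.915 = 77% by month 36.
- From 47%: S(36) = 0.47^1.5 = 0.322 and S(72) = 0.47^3 = 0.104. Shares: 0.530/0.896 = 59% and 0.678/0.896 = 76%.

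Other assumptions give this range. For a hazard halved after month 24, S(36) = S(24)^1.25 and S(72) = S(24)^2; for one cut to a quarter, S(24)^1.125 and S(24)^1.5. For the last row, S(24) = 0.5^(1/3) = 0.794 and S(36) = 0.5^(1/2) = 0.707, so the shares are 0.206/0.5 and 0.293/0.5.

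| Assumption | By month 24 | By month 36 |
|---|---|---|
| Nobody NEDA-free at month 72 (floor on the 2-year rates) | 53-56% | at least 53-56% |
| Constant hazard from the 2-year rates | 59-61% | 76-77% |
| Hazard halved after month 24 | 68-69% | 78-80% |
| Hazard cut to a quarter after month 24 | 78-79% | 84-85% |
| 50% nonresponders read as the 6-year figure, constant hazard | 41% | 59% |

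If redosing opens after 3 years, more than half of the failures come first in every row. If it opens at month 24, that holds in every row but the last.

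**4. What Tv covers.** Its stated target is disease activity, which the Objective lists separately from the need to redose. A sample may be drawn at the exacerbation itself, and relapse is one of the two redosing indications, so such a sample is concurrent and not a forecast. Tv pools exacerbation, switch and redosing. Nothing restricts it to the period after the second course.

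**5. What is scheduled at month 24.** End Points and Outcomes places lymphocyte subsets, serum neurofilament, DNA methylation and RNA collection at month 24, with MRI and BICAMS yearly. At month 36 there is no scheduled methylation or RNA sample.

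**The case against.** The strongest reply is that the plan contains more than a single 6-year label. Tv is sampled before redosing, is a preliminary end point and is compared with stable disease. Since the indication for redosing is itself relapse or new MRI activity, markers of disease activity bear on the need to redose. Association Modeling also uses repeated binary outcomes in mixed models, with lagged or leading covariates. This stands to the extent that a reader might infer that NEDA from screening is the only analysis serving the aim, or that the study cannot show anything about it. The article does not support either inference. What remains is that lagged covariates change the predictors and not the outcome, that no model is limited to the period after the initial courses, and that Tv has the limits in step 4.

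A second reply is that such detail belongs in the statistical analysis plan, which is not shown. That would hold if the article were silent; it instead fixes one end point for all outcome measures.

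Third, a reader might infer that the label is mostly settled before redosing under every assumption. The last row of the table shows otherwise if redosing opens at month 24.

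Fourth, a reader might suppose that actual redosing will be the outcome, and object that patients with the same activity who switch would count as having no need. No passage proposes that analysis, so no loss of power from it can be charged to this plan. Nor does the article say that its NEDA models will be reported as predicting reinitiation: Association Modeling describes its signature as predictive of treatment response. The mismatch is with the aim in the Objective and the Abstract.

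**Conclusion.** The point holds in this form: the need to redose is a named prediction target without an outcome, and the end point fixed for all measures is a poor substitute. On the article's 2-year rates, 53-56% of patients have lost NEDA 3 by month 24, about 59-61% of all 72-month failures under a constant hazard. The least favourable reading gives 41% by month 24 and 59% by month 36. The planned Tv comparison and lagged covariates reduce the gap but do not close it.

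The shares rest on three assumptions: that NEDA counted from screening cannot be regained, that the earlier trial's rates carry over to a cohort with fewer entry restrictions and more varied prior treatment, and the stated hazard shapes. The absence of a matching outcome depends on none of these. This should be corrected before the final analysis; it does not affect the estimate of the NEDA 3 proportion itself.

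**What to change.** For the redosing aim, add a landmark analysis at month 24:
- Include all patients still followed and not on another DMT, whatever their earlier NEDA status.
- Use only predictors measured at or before month 24.
- Take as outcome the first relapse or new MRI activity after month 24, which is the plan's own indication, whichever treatment follows.
- Treat a switch without prior activity as a competing or censoring event, with a sensitivity analysis because such censoring may be informative.

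Report the NEDA-from-screening models as results on treatment response only. Keep the Tv comparison as supporting evidence, separating samples taken at an exacerbation from those taken before a switch or redosing.

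The landmark should not be placed later, at a 3-year opening of redosing. A patient active between months 24 and 36, then redosed and stable, would be scored as having no need. The same could happen to a patient redosed at month 24 itself for earlier activity, if that is when redosing opens. The passages on the opening date in Study Design and Principal Findings must therefore be reconciled.

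Cost: analysis wording and one further model on visits already scheduled, although RNA is only stored pending funding. There will be fewer events than under the 6-year label, so wider intervals. As an illustration, at a two-sided 5% level and 80% power, the detectable standardised difference is (1.96 + 0.84) × √(1/n1 + 1/n2). This is 0.511 for 60 v 60, 0.543 for 40 v 80 and 0.591 for 30 v 90; the last two splits are assumed.
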